# Implementation and Evaluation of a Best Practice Advisory to Reduce Inequities in Technology Use for People With Type 1 Diabetes: Protocol for a Mixed Methods, Nonrandomized Controlled Trial

**DOI:** 10.2196/71038

**Published:** 2025-05-28

**Keywords:** equity, disparities, continuous glucose monitor, automated insulin delivery system, insulin pump, type 1 diabetes, best practice advisory, practice advisory, clinical decision support

## Abstract

**Background:**

Continuous advancements in diabetes technologies have improved self-management for people with type 1 diabetes. Continuous glucose monitoring and automated insulin delivery systems have enhanced the quality of life and glycemic outcomes while reducing severe hypoglycemia and diabetes ketoacidosis hospitalizations. Despite these benefits, racial inequities in the use of advanced diabetes technology (ADT) persist.

**Objective:**

This study aims to develop and evaluate a best practice advisory (BPA) within the electronic medical record (EMR) to reduce racial and ethnic disparities in ADT use. We hypothesize that an EMR-based BPA designed to standardize the prescribing of ADTs will minimize racial and ethnic disparities in ADT adoption or progression in use among pediatric and adult people with type 1 diabetes.

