Health IT (HIT) has the potential to address racial inequities in the prescribing and use of ADTs. HIT tools within the electronic medical record (EMR) include computerized provider order entry, clinical decision support (CDS) systems, patient communication portals, population health tools, and data warehouse tools among others. Recommendations for using HIT to reduce racial disparities include the standardized collection and use of race and ethnicity data, identifying inequities, tailoring quality improvement efforts, developing CDS systems for areas with significant disparities, and including input from racial and ethnic minorities in developing HIT tools [22]. CDS systems have been demonstrated to reduce racial disparities for multiple clinical conditions, including venous thromboembolism prophylaxis [23], chronic disease management [24-26], and HIV screening [27]. For example, a CDS intervention in people with heart failure led to a significant increase in referrals and guideline-recommended testing for non-Hispanic Black and Hispanic patients [28]. Compared with manual approaches, computer-based CDS systems are more effective in improving clinical practice and patient outcomes [29,30]. Evidence supports the success of CDS tools in diabetes management, where automated recommendations have led to improved glycemic outcomes and better adherence to clinical guidelines.

This Best Practice Advisories to Reduce Inequities in Technology Use (“BPA-TECH”) study will develop and evaluate a best practice advisory (BPA), an informatics alert, aimed at reducing disparities in ADT use among people with T1D. To the best of our knowledge, no CDS systems have been specifically developed or evaluated to address disparities in T1D technology use in a multicenter study. This gap is significant given the substantial evidence demonstrating the magnitude of this disparity and its adverse impact on clinical outcomes. We hypothesize that an EMR-based BPA designed to standardize the approach to people with T1D selection and prescribing of ADTs will minimize racial disparities in ADT use and progression among pediatric and adult people with T1D. We propose testing this hypothesis through a nonrandomized matched-pair intervention study, assessing a center-wide intervention among 7 clinical centers participating in the T1DX-QI.

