##### BPA Design

Using a rule-based algorithm, the EMR-based BPA will be designed to recommend ADT prescriptions for people with T1D not already using an AID system, and this would also encompass an alert for people not using CGM (and thus not using AID). The specific functionality of the BPA will be guided by the thematic analysis of the stakeholder input obtained in phase 1. The function will generate a BPA if a patient is not using an AID system and will suggest to the provider to discuss and prescribe technologies for using an AID system.

The BPA design will be led by the study organizing committee with direct involvement and support from Epic IT analysts and developers at Johns Hopkins University. Iterative feedback will be obtained from the principal investigators at each of the participating intervention centers during the prototype development. Table 3 outlines the key considerations for the design team. Throughout the design process, Norman’s user-centered design principles will be applied to ensure the BPA is intuitive, user-friendly, and meets the needs of all stakeholders [35].

**Table 3 table3:** Key considerations for best practice advisory (BPA) design team.

Consideration	Descriptions
Stakeholder input	Incorporate thematic analysis of feedback from patients, caregivers, and health care providers.
Algorithm rules	Define criteria for triggering the BPA based on patient EMR^a^ data.
Workflow integration	Ensure BPA integrates seamlessly into the provider’s workflow.
Iterative testing	Conduct iterative testing and refinement based on feedback from pilot implementations.
Setting and restrictions	Consider the setting (ambulatory, inpatient, both) and specific locations such as endocrinology clinics, primary care clinics, or health-system wide.
Location in Epic	Determine the BPA’s location in Epic, such as Windows, BPA Navigator, or Flag in Storyboard.
Active versus passive	Decide between active (windows that appear in the user’s Epic workflow) and passive (appear within assigned locations that fit into the end user’s workflow) BPAs.
Clinician action	Specify actions clinicians can take, such as placing orders or referrals.
Triggering messages	Determine language in the BPA, including potential references to practice guidelines, explain the reason for the BPA, and suggest actions to be taken.
Iterative testing	Conduct iterative testing and refinement based on feedback from pilot implementations.

^a^EMR: electronic medical record.

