### Phase 2: Evaluation (Study Design)

Using a nonrandomized matched pair-intervention design (ie, controlled before-after study), we will compare the use of ADT following the BPA intervention among non-Hispanic Black and Hispanic people with T1D at 7 participating T1DX-QI centers. These will be matched with control non-Hispanic Black and Hispanic people with T1D at nonintervention T1DX-QI centers over a 12-month period. Both control and intervention centers have completed the EMR data mapping to the T1DX-QI, allowing for consistent outcome assessment across both groups. The study will consist of 2 distinct periods:

Baseline period (before): 12 months before deployment of the BPA at the intervention centers.Implementation period (after): 12 months after the deployment of the BPA at the intervention centers.

The before-after matched-pair intervention design allows for a real-world assessment of the BPA’s impact on ADT use while controlling for key confounders. Comparing ADT prescribing before and after BPA implementation within intervention sites and using matched controls from nonintervention centers, the design also accounts for site-specific prescribing patterns and secular trends. This quasi-experimental approach is practical for an EMR-based intervention and minimizes selection bias by matching key clinical and demographic variables.

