### Primary Outcome

The primary outcome will be progression in ADT use (as documented in the EMR) during the 12-month study period. For both intervention and control centers, a participant’s baseline ADT status will be ascertained in the 12-month period before deployment of the BPA intervention. The primary outcome will be defined as positive for an individual if any of the following transitions from the baseline period to the implementation period occur with respect to ADT:

No CGM → CGM.No AID → AID.

The T1DX-QI database includes variables that will be used to evaluate the study outcome (eg, medication list and flowsheet data). We have extensively published on the T1DX-QI data source and its validation, and have used the database for several real-world studies [36-42].

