### Analysis

#### Phase 1

For survey data, Likert scale responses will be coded numerically for qualitative analysis. Descriptive statistics will be calculated to summarize the data, and differences between groups (ie, based on demographic variables) will be explored. For the structured interviews and focus groups, a thematic approach will be used to identify, analyze, and report patterns with the qualitative data. NVivo software will be used, which provides features for coding, organizing, and visualizing data [43]. Both deductive and inductive coding methodologies will be used to link similar codes to broader themes based on significant phrases, concepts, and ideas present in the transcripts [44]. Themes will be reviewed and refined through discussions among the research team to ensure consistency and reliability.

#### Phase 2

The primary outcome will evaluate the impact of the BPA intervention on patients’ progression of ADT use using a generalized linear mixed model to account for matched pairs and random center effects. The model will be adjusted for the number of encounters and other possible confounders not already matched.

The secondary outcome analyses will compare differences in ADT use between non-White and White people with T1D in the intervention and control groups. Additional secondary and exploratory outcomes will be assessed using the appropriate statistical model for the outcome adjusting for patient- and center-level confounders. Exploratory analysis assessing pediatric and adult centers separately will be performed.

In cases where ADT is not prescribed by the provider, we will explore the reasons why, and why the diabetes technology was not offered or accepted by patients. We will quantify the BPA responses as provider-led or patient-led reasons for not advancing ADT use. We will perform multivariable logistic regression analysis to evaluate whether patient characteristics (demographics, race, ethnicity, diabetes characteristics, and complications) are associated with the reasons that technologies are not offered or declined.

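### The hypothesis is a smaller racial gap, but the primary analysis has no between-race contrast, so a positive primary result does not show that the gap narrowed

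*Protocol article*

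**What the plan says.** - **Hypothesis.** The Abstract (Objective) states: "We hypothesize that an EMR-based BPA designed to standardize the prescribing of ADTs will minimize racial and ethnic disparities in ADT adoption or progression". The Introduction repeats it and continues: "We propose testing this hypothesis through a nonrandomized matched-pair intervention study".
- **Primary comparison.** Phase 2: Evaluation says "we will compare the use of ADT following the BPA intervention among non-Hispanic Black and Hispanic people with T1D at 7 participating T1DX-QI centers", and that these people will be "matched with control non-Hispanic Black and Hispanic people with T1D at nonintervention T1DX-QI centers".
- **Endpoint and model.** Primary Outcome: "The primary outcome will be progression in ADT use (as documented in the EMR) during the 12-month study period", counted per person as a move from no CGM to CGM or from no AID to AID. The Phase 2 analysis estimates the effect "using a generalized linear mixed model to account for matched pairs and random center effects", adjusted for encounters and unmatched confounders. No race-by-group term is named.
- **Where the gap appears.** The same section makes the comparison of non-White and White people, in both groups, a secondary analysis. The Discussion (Principal Findings) expects a smaller gap in addition to higher progression.
- **Trigger.** BPA Design: "The function will generate a BPA if a patient is not using an AID system". It has no race criterion, and the final functionality awaits phase 1.
- **Population and matching.** The Abstract's Results and Phase 2: Evaluation describe about 3000 non-Hispanic Black and Hispanic people and matched controls. The eligibility criteria have no race restriction, Intervention Group assigns about 11,496 eligible people, and Control Group matches intervention-group patients with race and ethnicity among the covariates.

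**The concern.** A disparity is a difference between race groups, and a disparity effect is a change in that difference. The primary analysis estimates something else: the difference between arms in progression, either within minority patients or, if Intervention Group sets the population, within all eligible patients. Neither reading contrasts races.

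Because the alert as written applies to everyone not using AID, uptake among White patients can also rise, by less, as much or more. The primary estimate in minority patients would be the same in each case. What is at stake is the main claim: a significant primary result could be taken as support for a disparity hypothesis that it does not test. The analysis that does address the gap uses different race groups from the primary. Whether its White patients have matched controls depends on which section governs the matching.

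**Working it through.** **The plan's own figure.** The Power section gives 589 matched pairs for 90% power at a 5-point difference. This concerns intervention versus control progression; no figure is given for the gap. An unpaired 1:1 calculation for 15% against 20% gives 1212 pairs (two-sided 5%). A paired calculation reaches 589 only with a discordant proportion of about 0.141, which is not stated. Since alpha, sidedness and within-pair correlation are not given, 589 cannot be called wrong, and nothing below depends on it except the last power figure.

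**1. Can the gap widen when the primary is positive?** Inputs: control progression 15% and a 5-point increase (Power). Assumed: a White control rate of 20%, 25% or 30%, and the same odds ratio in White patients.

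Odds ratio = (0.20/0.80)/(0.15/0.85) = 1.417.

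White rate with BPA = 1.417 × odds/(1 + 1.417 × odds).

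| White control rate | White rate with BPA | Gap, control | Gap, BPA | Change |
|---|---|---|---|---|
| 20% | 26.2% | 5.0 | 6.2 | +1.2 |
| 25% | 32.1% | 10.0 | 12.1 | +2.1 |
| 30% | 37.8% | 15.0 | 17.8 | +2.8 |

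Without the constant odds ratio, any direction is possible. With White patients going from 25% to 28%, the gap narrows from 10 to 8 points; to 30%, it stays at 10; to 35%, it widens to 15. The minority comparison is 15% against 20% throughout.

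**2. Progression gap versus gap in overall use.** AID users at baseline are excluded, so progression is measured among non-users. As a simplification, take AID use alone, with assumed baseline use of 50% in White and 25% in minority patients, and the progression rates of the 25% row.

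- Control: White 50 + 50 × 0.25 = 62.5%; minority 25 + 75 × 0.15 = 36.25%; gap 26.25 points.
- BPA: White 50 + 50 × 0.321 = 66.0%; minority 25 + 75 × 0.20 = 40.0%; gap 26.0 points.

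At baselines of 40%/20% the gap in use widens by about 0.25 points; at 60%/30% it narrows by about 0.7. So a 2.1-point widening in progression can leave the gap in use almost unchanged.

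**3. Can the data support a gap contrast?** Inputs: 3000 minority intervention patients (Abstract, Results), and 11,496 − 3000 = 8496 other eligible people (Intervention Group). Assumed: 50 to 100% of these are White (nW = 4248 to 8496), k = 1 to 4 controls per patient, variances from 20% and 30% (intervention) and 15% and 25% (control), and no correlation within matched sets.

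SE = √[0.20×0.80/3000 + 0.30×0.70/nW + 0.15×0.85/(3000k) + 0.25×0.75/(k·nW)]

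- k = 4, nW = 8496: SE 0.97 points; detectable with 90% power (× 3.24, two-sided 5%) 3.1 points.
- k = 1, nW = 4248: SE 1.38 points; detectable 4.5 points.

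If the gap varies between centers with an assumed SD of 3 points, add 0.03² × (1/7 + 1/41) = 0.000151 to the variance (7 intervention centers; 41 control centers from the Results section). The detectable change becomes 5.1 to 6.0 points.

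**4. At the stated 589.** Take four equal cells, minority 15% and 20%, White 25% in both arms. The variances sum to 0.1275 + 0.16 + 0.1875 + 0.1875 = 0.6625, so SE = √(0.6625/589) = 3.35 points. Power for a 5-point gap change is Φ(5/3.35 − 1.96), about 32%. For 90% power about 2785 per cell are needed.

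**The case against.** The strongest reply is that the disparity contrast is already planned. It is the first secondary analysis and the only one described specifically, and the Discussion lists higher progression and a smaller gap as two separate expectations. The Introduction assigns the hypothesis to the study, not to the primary test, and putting the effect in the target population first is a defensible order. This stands: the contrast is not absent, and the fault is one of alignment.

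Several stronger readings are tempting, and the document does not support them.

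- **That White patients have no matched controls.** This follows only if Phase 2: Evaluation governs. Under Intervention Group and Control Group they would be matched.
- **That a race-neutral alert is a flaw.** The Introduction names provider bias as a barrier, and a standardized rule is a reasonable response to it. The trigger matters here only because it leaves the direction of the gap open.
- **That the BPA is likely to widen the disparity.** The widening rests on assumed White rates and a constant odds ratio, and it largely disappears on the scale of overall use.
- **That the plan fails because the secondary is unranked or has no effect scale.** Such details commonly belong in an analysis plan, which is not shown.

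What the reply does not remove is that the Introduction says the matched-pair study tests the disparity hypothesis, while the primary comparison in that study cannot do so.

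**Conclusion.** The point holds in a limited form. The stated hypothesis concerns a gap between races, and the primary analysis has no contrast between races under either reading of its population. A positive primary result would show increased progression in the people analysed and nothing about the gap. The existing secondary can carry the disparity claim, but it compares non-White with White people where the primary concerns non-Hispanic Black and Hispanic people, and the sections conflict on whether White patients are matched.

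The size is illustrative. Under the assumed rates the progression gap could widen by 1.2 to 2.8 points while the primary is positive, with little change in overall use. The contrast is feasible if all eligible people are analysed (detectable change about 3 to 4.5 points, or 5 to 6 with the assumed center variation), but not at 589 per cell. These figures also rest on the assumed White share and on the control pool supplying the matches.

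**What to change.** 1. Limit the conclusion from the primary outcome to increased progression among the non-Hispanic Black and Hispanic people analysed.
2. Define the existing secondary as the between-arm difference in the White-minus-minority gap, on the absolute risk scale, with the race and ethnicity groups of the primary comparison and with the gap allowed to vary by center. Report the gap in overall ADT use beside it, since progression among non-AID users can move differently.
3. Reconcile the Abstract's Results and Phase 2: Evaluation with Intervention Group and Control Group, so that eligible non-Hispanic White patients are matched by the same procedure, at whatever ratio the control pool allows.
4. Claim reduced disparity only if that contrast supports it.

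The cost is some wording in the protocol and analysis plan and one more matched set from data already sent to the coordinating center. The downside is a narrower claim from the primary result.

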**Methods:**

The Best Practice Advisories to Reduce Inequities in Technology Use (BPA-TECH) study will use a nonrandomized matched pair intervention design. Phase 1 will use qualitative methods to develop and refine the BPA, including focus groups and surveys of health care providers and people with type 1 diabetes or their caregivers. Phase 2 will evaluate the effectiveness of the BPA through a controlled before-after study of people with type 1 diabetes seen at 7 T1D Exchange Quality Improvement Collaborative (T1DX-QI) centers, with control people with type 1 diabetes matched from nonintervention T1DX-QI centers. The baseline and postintervention periods will be the 12 months before and 12 months after deployment of the BPA at the intervention centers, respectively. Eligibility criteria include people with type 1 diabetes aged ≥2 years with an EMR diagnosis of T1D during the baseline period. The primary outcome is the progression in ADT use from the baseline to postintervention periods.

**Results:**

This 3-year study began in July 2024, with data collection from key stakeholders for phase 1 qualitative research beginning in August 2024. For phase 2, we estimate approximately 3000 eligible non-Hispanic Black and Hispanic people with type 1 diabetes at the intervention centers and 15,000 matched controls. Data on ADT use, glycated hemoglobin (HbA_1c_), severe hypoglycemic events, and diabetes ketoacidosis events will be collected via the T1DX-QI coordinating center. The study is powered to detect a between-group difference of 15% in the proportion of patients in the intervention and control groups in meeting the primary endpoint. We anticipate the completion of this study by May 2027.

**Conclusions:**

The BPA-TECH study aims to leverage health IT to address racial and ethnic disparities in ADT use among people with type 1 diabetes. By standardizing the approach to ADT prescribing for people with type 1 diabetes, the BPA-TECH has the potential to promote equity in diabetes management and improve clinical outcomes. The outcomes of this study will inform future efforts to reduce health care disparities.

**Trial Registration:**

ClinicalTrials.gov NCT06931275; https://clinicaltrials.gov/search?term=NCT06931275

**International Registered Report Identifier (IRRID):**

DERR1-10.2196/71038

## Introduction

Over the past decade, continuous advancements in diabetes technologies have helped to ease the burden of diabetes self-management for people with type 1 diabetes (T1D). Continuous glucose monitors (CGM) and automated insulin delivery (AID) systems have not only led to improved quality of life but also better glycemic outcomes and reduced incidence of hospitalizations for severe hypoglycemia and diabetic ketoacidosis (DKA) [1,2]. Given these clinical benefits, the American Diabetes Association now recommends that CGM be considered the standard of care for all people with T1D and that AID systems be recommended to people with T1D who are capable of safely using them [3].

Despite proven clinical benefits, racial inequities in the use of advanced diabetes technologies (ADTs), such as AID systems and CGMs, persist in both children and adults with diabetes [4-8]. Compared with Non-Hispanic White people with T1D, Non-Hispanic Black people with T1D have 1.5% higher glycated hemoglobin (HbA_1c_) levels on average [9] and are more than 3 times as likely to be hospitalized for hypoglycemia or DKA [10,11], yet they are half as likely to be using ADTs [12].

Factors contributing to these disparities include individual barriers like cost concerns, insertion pain, and alarm anxiety [13-16], as well as provider-level barriers such as insufficient knowledge, bias, and clinical decision-making criteria that do not align with current guidelines [17-19]. System-level barriers include insurance coverage issues and complicated processes for obtaining devices [20,21]. For example, a recent 7-year study at a large academic medical center found significantly lower rates of CGM discussions and use among Black people with T1D compared with their White counterparts, even after adjusting for various other factors [6]. In addition, a study by the T1D Exchange Quality Improvement Collaborative(T1DX-QI) highlighted the presence of implicit racial bias in approximately one-third of endocrinologists when prescribing ADTs [19].

Health IT (HIT) has the potential to address racial inequities in the prescribing and use of ADTs. HIT tools within the electronic medical record (EMR) include computerized provider order entry, clinical decision support (CDS) systems, patient communication portals, population health tools, and data warehouse tools among others. Recommendations for using HIT to reduce racial disparities include the standardized collection and use of race and ethnicity data, identifying inequities, tailoring quality improvement efforts, developing CDS systems for areas with significant disparities, and including input from racial and ethnic minorities in developing HIT tools [22]. CDS systems have been demonstrated to reduce racial disparities for multiple clinical conditions, including venous thromboembolism prophylaxis [23], chronic disease management [24-26], and HIV screening [27]. For example, a CDS intervention in people with heart failure led to a significant increase in referrals and guideline-recommended testing for non-Hispanic Black and Hispanic patients [28]. Compared with manual approaches, computer-based CDS systems are more effective in improving clinical practice and patient outcomes [29,30]. Evidence supports the success of CDS tools in diabetes management, where automated recommendations have led to improved glycemic outcomes and better adherence to clinical guidelines.

This Best Practice Advisories to Reduce Inequities in Technology Use (“BPA-TECH”) study will develop and evaluate a best practice advisory (BPA), an informatics alert, aimed at reducing disparities in ADT use among people with T1D. To the best of our knowledge, no CDS systems have been specifically developed or evaluated to address disparities in T1D technology use in a multicenter study. This gap is significant given the substantial evidence demonstrating the magnitude of this disparity and its adverse impact on clinical outcomes. We hypothesize that an EMR-based BPA designed to standardize the approach to people with T1D selection and prescribing of ADTs will minimize racial disparities in ADT use and progression among pediatric and adult people with T1D. We propose testing this hypothesis through a nonrandomized matched-pair intervention study, assessing a center-wide intervention among 7 clinical centers participating in the T1DX-QI.

